Proportion of patients who die, develop respiratory failure (requiring non-invasive ventilation, high-flow oxygen devices or invasive mechanical ventilation) between baseline and Day 15 will be compared using a logistic mixed model to take into account stratification factors (duration of symptoms prior to enrolment and sites).

Secondary hypotheses have been ordered according to relative importance.

The key secondary outcome, which is the proportion of patients who die, develop respiratory failure (requiring non-invasive ventilation, high-flow oxygen devices or invasive mechanical ventilation) between baseline and Day 8 and Day29 will be analysed as the primary endpoint.

Others secondary endpoint :

Quantitative endpoint will be compared using linear mixed model and qualitative data with logistic mixed model to take into account stratification factors.

Time data’s will be analyzed using survival model (Kaplan-Meier, Cox model). Fine & Gray method will be used to take into account competing risk.

Safety Analyses

The safety population is defined as all subjects randomized into the study but excluded who are ineligible at baseline or who have not had any dose of treatment.

Safety endpoints include death through Day 29 and through Day 60, SAEs and Grade 3 and 4 AEs. These events will be analyzed univariately. Time-to-event methods will be used for death. Each AE will be counted once for a given subject and graded by severity and relationship to COVID-19 or study intervention. AEs will be coded using the current version of the Medical Dictionary for Regulatory Activities (MedDRA). AEs will be presented by system organ class, duration (in days), start- and stop-date. Adverse events leading to premature discontinuation from the study intervention and serious treatment-emergent AEs will be presented either in a table or a listing.

More details will be described in the Statistical Analysis Plan.

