### Choice of subjects to be included in analysis

The safety population included all subjects randomized into the study who received at least one dose of study drug.

For phase 2 a:

The intent-to-treat (exposed, ITT[E])Population is defined as all subjects who met study criteria and were randomized into the study with documented evidence of having received at least one dose of randomized treatment and at least one post-baseline XAV-19 IgG SARS-CoV2 titers measurement.

The Per-Protocol Population is defined as all subjects included in the ITT(E) Population excluding those who had at least one major protocol deviation.

For phase 2 b:

The intent-to-treat (ITT) Population is defined as all subjects randomized into the study.

The Full Analysis Set population includes the ITT population but excludes subjects who are ineligible at baseline. Patient with withdrawal of consent will be conserved in the full analysis set

The Per-Protocol Population is defined as all subjects of the full analysis set population which received at least one dose of randomized treatment excluding those who had at least one major protocol deviation.

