### Methods and schedule envisaged to measure, compile and analyse safety evaluation parameters

Any AR/AE whether expected or unexpected, serious or not, must be real-time collected in the study eCRF.

Safety assessment will be followed at each visit.

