## Protocol deviations

The following protocol deviations are pre-defined as major protocol violations with a direct bearing on primary outcome:

- Patients who did not respect treatment scheduled (i.e. for who treatment was not administrated or not entirely administrated)

- Patients who did not received the allocated treatment (treatment cross-over)

- Patients who did not verify all major inclusion criteria and all major non-inclusion criteria

- Patients lost to follow-up before day 15

- Patients who withdrew their consent before day 15

- Patients who had a respiratory failure before treatment administration

Protocol deviations will be identified and classified as major or minor in blind reviews before the database freezing. The number and % of patients with major and minor protocol deviations will be provided by treatment group, with details of the type of deviation. No formal statistical comparison will be done.

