## Population definition

**Intent-to-treat (ITT) Population**: The ITT population will include all randomized patients, regardless of their eligibility and any protocol deviations, according to the treatment group to which they were assigned at randomization.

**Modified Intent-to-treat (mITT) Population**: The mITT population will include the ITT population but will exclude:

1. Patients who did not received treatment for any reason (withdrawn consent or investigator decision due to quick worsening of respiratory status before administration)
2. Patients with legal requirements (i.e. guardianship or trusteeship, < 18 years, no signed consent).

**Per-protocol (PP)**: The PP population will include the mITT population but will exclude:

1. Patients with treatment cross over, defined as receiving the other treatment
2. Patients with withdrawn consent between D1 and D15
3. Patients with major inclusion or non-inclusion criteria violation
4. Patients with major protocol deviations listed in section 3.2

The primary endpoint and the key secondary endpoints will be analysed on the ITT, mITT and the PP population.

The other secondary endpoints will be analysed on the mITT population only.

**Safety population**: The safety population will be included all randomized patients who have received the study treatment or placebo.

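### Protocol 7.2.1 leaves dosed but ineligible patients out of the Phase 2b safety population, while protocol 7.2.6 and SAP 3.3 keep them in

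*Combined protocol and SAP*

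**What the plan says.** Three places define the population for the Phase 2b safety tables.

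- **Protocol 7.2.1, Phase 2b, Safety Analyses.** All randomised subjects, "excluded who are ineligible at baseline or who have not had any dose of treatment".
- **Protocol 7.2.6, opening sentence, above the separate Phase 2a and Phase 2b headings.** "The safety population included all subjects randomized into the study who received at least one dose of study drug".
- **SAP 3.3.** "The safety population will be included all randomized patients who have received the study treatment or placebo".

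The following bear on how these should be read:

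- In 7.2.6 an eligibility exclusion does appear for Phase 2b, but for a different set: "The Full Analysis Set population includes the ITT population but excludes subjects who are ineligible at baseline".
- SAP 3.2 foresees ineligible patients among those randomised and lists them as a major deviation: "Patients who did not verify all major inclusion criteria and all major non-inclusion criteria".
- Protocol 8.2.2 requires event collection whatever the analysis set: "Any AR/AE whether expected or unexpected, serious or not, must be real-time collected in the study eCRF".
- The statistical methods text of 7.2.1 ends by deferring to the SAP: "More details will be described in the Statistical Analysis Plan". SAP 1.1 limits the SAP to Phase 2b.

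**The concern.** A safety population is normally defined by exposure. The 7.2.1 sentence makes it depend on exposure and on eligibility, so a patient who was randomised, infused and later judged ineligible belongs to it under one rule and not under the other two. The protocol disagrees with itself here, even before the SAP is opened.

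At stake is who is counted in the adverse event and serious adverse event tables and in the comparison of arms. Some Phase 2b exclusion criteria bear directly on tolerance of the product, such as known hypersensitivity to it or an earlier grade 3 allergic reaction to plasma transfusion. Hypersensitivity and infusion reactions are named safety endpoints. A patient dosed despite such a criterion is informative for safety and should be in the tables. The 7.2.1 wording also refers to ineligibility in general, without the restriction to major criteria used in SAP 3.2, so it could reach further than the SAP's deviation list.

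**Working it through.** **1. The definitions as sets.** Let R be randomised, D dosed (XAV-19 or placebo) and E eligible at baseline.

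- Protocol 7.2.1: R and D and E
- Protocol 7.2.6: R and D
- SAP 3.3: R and D

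| Randomised patient | 7.2.1 | 7.2.6 | SAP 3.3 |
|---|---|---|---|
| Dosed, eligible | in | in | in |
| Dosed, ineligible | **out** | in | in |
| Not dosed, eligible | out | out | out |
| Not dosed, ineligible | out | out | out |

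The definitions differ in one row only. The Phase 2a part of 7.2.1 also uses the exposure-only rule, so the Phase 2b sentence is the outlier.

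**2. Where those patients are still counted.**

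- *Collection and reporting:* all events go into the eCRF (protocol 8.2.2, 8.4.1), and serious ones go to the sponsor immediately (8.4.3).
- *DSMC thresholds:* the counts of ventilated or dead patients are set against patients included, with no eligibility filter (protocol 6.7.3 and the SAP's stopping guidance).
- *Primary and key secondary endpoints* (death or respiratory failure to Days 15, 8 and 29): analysed on ITT, among other sets (SAP 3.3). ITT keeps everyone randomised.
- *Mortality at Days 15, 29 and 60:* analysed on mITT (SAP 3.3). That set drops the untreated and those failing a legal requirement (guardianship or trusteeship, under 18, no signed consent). Other dosed but ineligible patients remain.

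The loss under 7.2.1 would therefore fall on the safety summaries and the between-arm safety comparisons.

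**3. The denominator.** The documents state no size for the safety population. The only available figure is the planned 398, which reproduces. For 20% versus 10%, two-sided 5%, 80% power, pooled variance and no continuity correction:

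n per arm = [1.960·√(2·0.15·0.85) + 0.842·√(0.20·0.80 + 0.10·0.90)]² / 0.10² = (0.990 + 0.421)² / 0.01 ≈ 199, so 398 in total.

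Nothing in this point depends on that calculation; 398 serves only as an upper limit for the number dosed.

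**4. Illustrative size.** The ineligible share f is not in the documents. Assume that all 398 are dosed.

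| Assumed f | Patients removed by 7.2.1 | Safety set left |
|---|---|---|
| 1% | 0.01 × 398 ≈ 4 | 394 |
| 2% | 0.02 × 398 ≈ 8 | 390 |
| 5% | 0.05 × 398 ≈ 20 | 378 |

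Assume further that each removed patient independently has a serious event with probability q. The chance that at least one such patient is omitted is 1 − (1 − q)^n:

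| n removed | q = 5% | q = 20% |
|---|---|---|
| 4 | 19% | 59% |
| 8 | 34% | 83% |
| 20 | 64% | 99% |

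Both f and q are assumptions.

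**5. Direction of the effect on rates.** Write r_E and r_I for the event rates in eligible and ineligible dosed patients. The exposure-only rate is (1 − f)·r_E + f·r_I and the 7.2.1 rate is r_E. They differ by f·(r_I − r_E), which is one hundredth of the gap at f = 1% and one twentieth at f = 5%. Its sign is that of r_I − r_E, on which the documents are silent.

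**The case against.** The strongest reply is that the SAP settles the matter. It covers Phase 2b only, 7.2.1 hands the detail to it, and its definition is the inclusive one. With 7.2.6, two of three places already state the rule asked for, and an analyst working from the SAP would omit nobody. This stands as mitigation and is why the severity is modest. It does not remove the defect. No precedence rule is stated, the SAP does not flag its definition as a departure from 7.2.1, and protocol 7.2.5 expects no change to the analysis strategy. The two protocol sections also conflict without any reference to the SAP.

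A second reply is that the affected group may be very small. Eligibility must be confirmed before randomisation (protocol 6.2.2), and SAP 3.3 foresees randomised patients who are never treated, so fewer than 398 may be dosed. This stands: the count could be close to zero.

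A reader might infer something stronger, namely that the sentence hides adverse events, or that it understates harm because ineligible patients are sicker and an eligibility review would pick which events count. The documents do not support this:

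- Events are collected and reported regardless of analysis set, and deaths and respiratory failures in these patients remain in the ITT analyses.
- Some criteria mark higher-risk patients, but others (French social security cover, contraception, time since symptom onset, participation in another trial) need not. Removing a patient also reduces numerator and denominator together, so the direction is open.
- SAP 3.2 has deviations identified and classified under blind before the database is frozen, which guards against exclusion that depends on arm.

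**Conclusion.** The sentence in protocol 7.2.1 is wrong as written. It adds an eligibility condition to the Phase 2b safety population that protocol 7.2.6 and SAP 3.3 do not have and, if followed, it would leave exposed patients out of the safety summaries and comparisons. The contradiction rests on the text alone and needs no assumption.

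The size is unknown. The 4 to 20 patients are an illustration that assumes all 398 are dosed and 1% to 5% are ineligible, and no direction of bias can be claimed. Severity is modest, because the omission occurs only if 7.2.1 is followed over the SAP. The resemblance to the Full Analysis Set definition in 7.2.6 suggests that an efficacy-set exclusion was carried into the safety sentence, but the documents do not say so.

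**What to change.** In the Phase 2b safety paragraph of protocol 7.2.1, delete the exclusion for ineligibility at baseline. The population then matches 7.2.6 and SAP 3.3: every randomised patient given study drug or placebo, regardless of eligibility.

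A separate clarification is optional. SAP 3.2 foresees infusions that are not completed, yet neither 7.2.6 (at least one dose) nor SAP 3.3 (treatment received) says expressly that a partial infusion counts. If partially infused patients are to be counted explicitly, add the words any amount in all three places. This would be new text, not a copy of either existing definition.

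The cost is one sentence in the protocol, or three short edits with the clarification. Sample size, power, efficacy sets and data collection are unchanged.

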### Statistical justification of the number of inclusions

Phase 2 a:

As it is a Phase 2 a, the number of patients was determined according to relevant publications of phase 2a. It was decided to enrol two cohorts of 8 patients (6 treated patients and 2 matching placebo in each cohort).

Phase 2 b:

Assuming a true treatment diminution in clinical failure rate of 10% for XAV-19 added to SoC therapy compared to placebo added to SoC therapy where a rate of 20% is expected, a sample size of 398 randomized participants provides at least 80% power that the primary analysis will be statistically significant at the two-sided 5% significance level.

The 20 patients of the open-label ancillary terminal study (150 mg dose of XAV-19) will not be included in the primary analysis. Their pharmacokinetic characteristics and variability will be compared to the parameters of randomized phase 2b patients taking part in the ancillary pharmacokinetics ancillary study and immunomonitoring ancillary study.

### Expected level of statistical significance

The degree of significance is set at 5%.

### Consideration method for missing, unused or invalid data

Phase 2a:

No imputation will be realized in this study.

Patient who did not receive both doses (first cohort phase 2a and first 2 patients of the second cohort of phase 2a) or one dose (6 last patients of the second cohort of phase 2a and phase 2b), according to protocol or followed up until D8 will be replaced.

Phase 2b:

No randomized subject replacement is planned.

We do not expect missing data for the primary outcome.

All attempts will be made to collect all data per protocol. Any data point that appears to be erroneous or inexplicable based on clinical judgment will be investigated as a possible outlier. If data points are identified as outliers, sensitivity analyses may be performed to examine the impact of including or excluding the outliers. Any substantive differences in these analyses will be reported.

For the primary outcome, if patient is not followed up until D15 then, data will be imputed by a multiple imputation procedure and a sensitivity analysis will be performed on the imputation method,

For the analyses of the secondary outcomes that involve clinical score (i.e. the key secondary outcome and time to improvement), if a subject is discharged from the hospital without a previously or concurrently reported clinical score of 2 or 1, then their clinical score at the time of discharge will be imputed as 2, which is the highest value for a non hospitalized subject.

For the analyses of the secondary outcomes, the following imputation rules will be used for subjects who are lost to follow-up, terminate early from the study, or do not have further outcome data available after discharge for any reason:

• Days of Non-invasive ventilation/high-flow oxygen:

If the subject’s clinical status scale is 5 at the last observed assessment, then the subject will be considered to be on non-invasive ventilation/high-flow oxygen. The endpoint will be total days when assessments are available plus all imputed days following the last observed assessment.

If the subject is not on non-invasive ventilation/high-flow oxygen at the last observed assessment, then the subject will be considered to not be on non- invasive ventilation/high-flow oxygen for the remainder of follow-up. Thus, no additional imputed days will be added to the number of days recorded on available assessments.

• Days of intubation or mechanical ventilation:

If the subject’s clinical status scale is 6 at the last observed assessment, then the subject will be considered to be on non-invasive ventilation/high-flow oxygen. The endpoint will be total days when assessments are available plus all imputed days following the last observed assessment.

If the subject is not on non-invasive ventilation/high-flow oxygen at the last observed assessment, then the subject will be considered to not be on non- invasive ventilation/high-flow oxygen for the remainder of follow-up. Thus, no additional imputed days will be added to the number of days recorded on available assessments.

• Days of ventilation/ECMO:

If the subject’s clinical status scale is 7 at the last observed assessment, then the subject will be considered to be on ventilation/ECMO through Day 29. The endpoint will be total days when assessments are available plus all imputed days following the last observed assessment.

If the subject is not on ventilation/ECMO at the last observed assessment, then the subject will be considered to not be on ventilation/ECMO through Day 29. Thus, no additional imputed days will be added to the number of days recorded on available assessments.

• Days of Oxygen:

If the subject’s clinical status score is 4, 5, 6, or 7 at the last observed assessment, then the subject will be considered to be on oxygen through Day 29. The endpoint will be total days when assessments are available plus all imputed days following the last observed assessment.

If the subject is not on oxygen at the last observed assessment, then the subject will be considered to not be on oxygen through Day 29. Thus, no additional imputed days will be added to the number of days recorded on available assessments.

• Days of Hospitalization

If the subject is discharged and no further hospitalization data are available, then the subject will be assumed to not have been readmitted. Thus, no additional imputed days will be added to the number of days recorded on available assessments. If a subject dies while hospitalized, the number of days of hospitalization will be imputed as 29 days.

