### Days of Ventilation/ECMO

Ventilator / ECMO days should be associated with the ordinal scale equal to 6 or 7.

The total number of days will be the sum of all reported days, regardless of whether the days occur consecutively or in disjoint intervals.

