### Days of invasive ventilation/ECMO:

If the subject’s clinical status scale is 6 or 7 at the last observed assessment, then the subject will be considered to be on ventilation/ECMO through Day 29. The endpoint will be total days when assessments are available plus all imputed days following the last observed assessment.

If the subject is not on invasive ventilation/ECMO at the last observed assessment, then the subject will be considered to not be on ventilation/ECMO oxygen for the remainder of follow-up. Thus, no additional imputed days will be added to the number of days recorded on available assessments.

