### Days of Hospitalization

If the subject is discharged and no further hospitalization data are available, then the subject will be assumed to not have been readmitted. Thus, no additional imputed days will be added to the number of days recorded on available assessments. If a subject die while hospitalized, the number of days of hospitalization will be imputed as 28 days.

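### Protocol 7.2.4 labels a patient last seen at score 6 as on non-invasive support and carries ventilation/ECMO days forward from score 7 only, in conflict with its own bullet heading, its endpoint list and the SAP

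*Combined protocol and SAP*

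**What the plan says.** Protocol 7.2.4 gives imputation rules for secondary outcomes in phase 2b patients who are lost to follow-up, leave early or have no further outcome data after discharge. Three bullets concern ventilatory support:

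- **Non-invasive ventilation/high-flow oxygen.** Days are carried forward if the "clinical status scale is 5 at the last observed assessment, then the subject will be considered to be on non-invasive ventilation/high-flow oxygen". No end day is stated. A patient not on that support when last seen gets no further days.
- **The bullet headed "Days of intubation or mechanical ventilation".** Its rule is that if the "clinical status scale is 6 at the last observed assessment, then the subject will be considered to be on non-invasive ventilation/high-flow oxygen". Its second limb, for patients who get no further days, is again worded in terms of non-invasive support. No end day is stated.
- **Ventilation/ECMO.** The rule is that if the "clinical status scale is 7 at the last observed assessment, then the subject will be considered to be on ventilation/ECMO through Day 29".

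The protocol's phase 2b secondary endpoints list only two durations of this kind: days of non-invasive ventilation or high-flow oxygen, and days of invasive mechanical ventilation/ECMO, both up to Day 29.

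SAP 5.1 ties non-invasive/high-flow days to score 5 alone and states: "Ventilator / ECMO days should be associated with the ordinal scale equal to 6 or 7". SAP 5.4 carries score 5 forward as non-invasive support to Day 29. For invasive support, if the "clinical status scale is 6 or 7 at the last observed assessment, then the subject will be considered to be on ventilation/ECMO through Day 29".

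For a patient who dies in hospital, protocol 7.2.4 sets hospital days to 29. In SAP 5.4, "the number of days of hospitalization will be imputed as 28 days".

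**The concern.** The score-6 paragraph reads like the score-5 paragraph with only the number changed. The heading above it concerns intubated patients, while the rule below it assigns them to non-invasive support. Because the ventilation/ECMO bullet then starts at score 7, no protocol rule clearly carries forward invasive-ventilation days for a patient last seen at score 6. Three protocol rules also do not map onto two listed endpoints.

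The patients concerned are among the sickest of those who lack later data. For them the protocol and SAP prescribe different values of a listed secondary endpoint. Protocol 7.2.1 leaves further detail to the SAP, but a different rule is not further detail. Protocol 7.2.5 expects no change to the analysis strategy, and the SAP does not flag the difference. Two written rules are therefore available for the same patient, and the choice between them should be fixed before unblinding.

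The hospital-days conflict is of the same kind: two values for the same death.

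**Working it through.** The documents state no figure for this imputation, so there is none to reproduce. The check applies each rule to the same patient.

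**Inputs.** The horizon is Day 29 (SAP 5.4, and the score-7 bullet of protocol 7.2.4). The day of the last observed assessment is d. Carried-forward days = 29 - d. The figure with the 8-point scale is not shown, so score 6 is taken as invasive ventilation on the strength of the protocol's own heading and SAP 5.1.

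**One patient, last score 6, d = 8**, so 29 - 8 = 21 days are at stake:

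| Rule | Added to ventilation/ECMO | Added to non-invasive/high-flow |
|---|---|---|
| SAP 5.4 | 21 | 0 |
| Protocol, first limb of the score-6 bullet taken literally | 0 | 21, if run to Day 29 |
| Protocol, second limb of the score-6 bullet, or the score-5 bullet | 0 | 0, since an intubated patient is not on non-invasive support |
| Protocol, device wording treated as a slip | 0 under the score-7 bullet; 21 if the score-6 and score-7 bullets are added together | 0 |

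The literal readings agree on 0 ventilation/ECMO days and disagree on the non-invasive column. The fourth row matches the SAP only if the two bullets are summed and the score-6 bullet also runs to Day 29. The protocol says neither.

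**Other days.** For d = 5, 10, 15 and 20, the ventilation/ECMO days missing against the SAP are 24, 19, 14 and 9.

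**Scores 5 and 7.** Both documents give the same days, provided that the protocol's score-5 rule also runs to Day 29.

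**Effect on an arm mean.** The documents give no number of such patients, so m is an assumption. The shift in mean ventilation/ECMO days is m × (29 - d) / 199:

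- m = 2, d = 8: 2 × 21 / 199 = 0.21 days
- m = 1, d = 10: 1 × 19 / 199 = 0.10 days
- m = 10, d = 10: 10 × 19 / 199 = 0.95 days

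**Effect on what the SAP reports.** SAP 5.2 summarises these durations by medians. The design expects 20% of placebo patients to reach respiratory failure or death by Day 15, so well under half of an arm should ever be ventilated. If never-ventilated patients count as 0, the median is then 0 under either rule. SAP 5.2 states that zero rule for non-invasive support but not for invasive support. A median taken among ventilated patients only could move. The between-group comparison is of time to first use (Fine & Gray), which carried-forward days do not change.

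**Endpoints not affected.** Oxygen days are the same, because both documents use scores 4 to 7. The primary endpoint is untouched, because SAP 5.1 counts any score from 5 to 8 as failure.

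**Hospital days at death.** The protocol gives 29 and the SAP 28, a difference of 1 day per in-hospital death. For a survivor still in hospital on Day 29, elapsed days are 29 - 1 = 28 and inclusive days are 29 - 1 + 1 = 29.

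**The case against.** The strongest reply is that this is a drafting slip which the SAP already resolves. The SAP covers phase 2b specifically, and its definitions and imputation rules agree with each other. Within the protocol, score 6 has its own bullet under a heading about intubation. The days it imputes naturally belong to that heading, and together with the score-7 bullet it covers the same scores as the SAP. Much of this stands: if the SAP rule is programmed, no days are wrong. It does not remove the point, because the protocol never says the two bullets are to be summed, lists one endpoint rather than two, and neither document says which prevails.

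Three stronger readings are tempting and are not supported:

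- **That the protocol moves 21 days into the non-invasive endpoint, so that two endpoints err in opposite directions.** That is one literal reading. The second limb of the same bullet and the score-5 bullet both point to 0 non-invasive days.
- **That the trial will report wrong ventilation days.** This follows only if the protocol rule, not the SAP rule, is the one applied.
- **That 29 hospital days for a death lies outside the scale.** Counted inclusively, D1 to D29 is 29 days, and the protocol states no counting rule. The value 28 is right only if the SAP's count from D1 to discharge is read as elapsed time.

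**Conclusion.** The conflict is real and should be corrected. As written, the score-6 bullet of protocol 7.2.4 contradicts its heading, and the ventilation/ECMO bullet omits score 6, against the protocol's endpoint list and against SAP 5.1 and 5.4. Read literally, the protocol gives 0 carried-forward ventilation/ECMO days where the SAP gives 29 - d, or 21 for a patient last seen on Day 8. The destination of those days under the protocol is ambiguous.

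The practical effect is limited to secondary duration endpoints in patients without later data. It is probably small on medians and nil if the SAP rule is used. The shifts in arm means rest on assumed numbers of affected patients. The hospital-days mismatch is a separate, certain conflict of one day per in-hospital death; the documents do not settle which value is right.

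**What to change.** 1. In protocol 7.2.4, replace the bullets for intubation/mechanical ventilation and for ventilation/ECMO by the single SAP rule: last score 6 or 7 counts as invasive ventilation/ECMO through Day 29. Keep score 5 alone for non-invasive/high-flow support and add the missing end day, Day 29.
2. Use one hospital-days value for in-hospital deaths in both documents and state the counting convention for survivors next to it: 28 if days are elapsed from D1, 29 if they are counted inclusively.
3. State which document prevails where they differ. If the protocol is not amended before unblinding, record in the SAP that its ventilation rule replaces the one in protocol 7.2.4.

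The cost is wording at the next amendment. No extra data are needed, and no reprogramming of the ventilation endpoints if the SAP rule is already coded. Choosing 29 hospital days would change one constant in the SAP.
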